#### Concealment mechanism (Spirit 16b)

Participants will be randomized after eligibility and written consent has been confirmed at visit 1 and baseline measurements have been completed (index participants) and visit 2 (household/whānau participants).

#### Implementation (Spirit 16c)

A member of the study team will log into the online system to seek randomization. The allocated arm will be recorded in the participant’s file and in the Site File.

### Assignment of interventions: blinding

#### Who will be blinded (Spirit 17a)

The Principal investigator, laboratory technicians and study statistician will be blinded.

#### Procedure for unblinding if needed (Spirit 17b)

Not applicable.

### Data collection and management

#### Plans for assessment and collection of outcomes (Spirit 18a)

In addition to clinical measurements and blood samples, data will also be collected using participant-completed questionnaires on paper and/or electronically through the study period (Table 5). Data will be collected during interviewer-led assessments at the relevant timepoints, and during the phone calls. Body composition using a DXA scan and/or BIA will be measured in index participants only.

#### Plan to promote participant retention and complete follow-up (Spirit 18b)

If randomized to the intervention, participants may opt out of intervention activities that are offered but remain enrolled in the study and continue with clinical assessments, complete questionnaires and allow researchers access to their medical records. Index and household/whānau participants will receive phone, text message or email reminders regularly to complete the questionnaires, depending on their preference.

#### Data management (Spirit 19)

When an index participant consents to take part, they will be allocated a unique participant identification number. A corresponding household/whānau participant will be allocated a unique participant identification number which connects to the identification number of their corresponding index participant. Consent forms and other paperwork containing personal identifiable data including completed paper questionnaires will be stored in a locked filing cabinet or password protected computer at each site. Data collected on REDCap will be stored within the REDCap system. Dietary intake data collected on Intake 24 is stored on that platform. Personal and research data entered directly onto a computer by participants or by a member of the research team will only be accessible to members of the research team. Participant details will be anonymized in all publications and other means of dissemination that result from the trial.

#### Confidentiality (Spirit 27)

The principles of confidentiality will be adhered to. Data will be collected and retained in accordance with the Privacy Act 2020 and the National Ethics Advisory Committee National Ethical Standards for Health and Disability Research and Quality Improvement. Personal data will be kept only for as long as it is required. All data analysis will take place on encrypted, password-protected computers. No data will be released to any unauthorized third party without the written approval of Principal Investigator. Data will be available for monitoring by the Health and Disability Ethics Committee or regulatory agencies if requested. An archiving plan will be developed for all study materials in accordance with the Sponsor’s archiving policy, and study materials will be archived for 10 years from the end of the trial. Access to the protocol, data and the statistical code will be available through application to the Principal Investigator once the primary manuscripts have been submitted.

#### Plans for collection, laboratory evaluation and storage of biological specimen for genetic or molecular analyses in this trial/future use

Analysis of blood samples will be limited to analytes that will give information on the cardiometabolic health of participants. This will include but are not limited to HbA1c, lipids, glucose, insulin and high sensitivity C reactive protein. Participants will be given the option to provide consent for their blood and fecal samples to be included in an anonymous manner in a biobank.

### Statistical analyses

The primary analysis will be conducted according to the intention to treat principle. Appropriate data descriptions and plots will be used for all variables. Change from baseline variables will also be described as paired differences but, in general, baseline values of response variables will be used as covariates in analyses rather than analyzing change from baseline. For RCT 1 and RCT 2 and for the index participants, the primary analysis for the primary outcome variable will be Analysis of Covariance (ANCOVA) with the baseline value of the MetSSS as a continuous covariate and the randomized treatment as the main explanatory variable. This strategy will also be used for all continuous outcome variables with the appropriate baseline value of any specific outcome variable as the covariate. The baseline measurement will be just before the relevant randomization. Normal distribution assumptions for residuals will be checked for models of continuous outcome variables and if these are badly violated transformations, such as a logarithm transformation, will be used. For some variables, outlined in Table 4, it is already established that the logarithm transformation is likely to be appropriate. Where appropriate transformations cannot be identified a rank-based procedure, the Mann–Whitney test with the Hodges-Lehmann estimator of location difference, will be used. For the primary outcome variable, the MetSSS, a sensitivity analysis will be a secondary analysis adjusting for possible confounding by important explanatory variables that may have not been evenly distributed by the randomization. These will be as a composite categorical variable for whether medication was changed for any of blood pressure control, glucose management, or lipid control; and separately, for physical activity assessed by the international physical activity questionnaire score. Analysis will be by ANCOVA with these confounding variables in addition to the baseline MetSSS and randomized treatment. Another secondary analysis will be to explore if randomized treatment allocation is associated with different effects in subgroups; using an appropriate treatment by subgroup interaction models. These subgroups are: age, sex, baseline diet adherence score, household size, and whether a household has children. For the continuous variables the analysis of the interaction will be on the continuous scale but for illustrative purposes, and for use in a Forest-like plot, will also be estimated for the first and third quartile of the continuous predictor distribution. Another important secondary analysis will be of all participants treating each household as a cluster and using a Mixed Linear model with baseline measurement and randomized treatment as fixed effects, and household clusters as random effects. If in the event there are very few clusters, the random effect may not be estimable and then this will be equivalent to ANCOVA. The Intraclass correlation coefficient for the clustering effect will be estimated directly from the variance components in the mixed linear models, should a cluster effect be estimable. Categorical and ordinal variables will be analyzed by logistic regression, the latter corresponding to ordinal regression, for the individual participant analysis, and by a Generalized Mixed Linear Model for all participants. There may be other effect modifiers that we will consider but these will be outlined in the Statistical Analysis Plan.

For the longitudinal cohort study stage, a similar ANCOVA strategy will be used for the final measurement of the continuous outcomes. A mixed linear model will also be used to examine linear trends in changes in outcomes by accounting for correlation between measurements in the same participants as well as the clustering effect for an analysis of all participants.

SAS version 9.4 will be used for analyses.

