**Methods and analysis:**

This is a multi-center, three-stage trial with two parallel group superiority randomized controlled trials (RCTs), and a longitudinal cohort study embedded within the trial design. The first RCT (RCT 1) is a comparison of the NZMedDiet pattern compared to usual diet for 12 weeks. The Behavior Change Wheel was used to select and implement strategies to support participant adherence to the NZMedDiet, such as web-based nutrition education on healthy shopping and cooking. The second (RCT 2) compares online social support to no online social support for 12 weeks, administered to participants immediately following RCT 1. The third stage is a longitudinal cohort study where all participants are followed from the beginning of their start of the active intervention for 12 months in total. The primary outcome measure for each stage is the metabolic syndrome severity score (MetSSS). The duration of enrolment is 12–15 months. The total recruitment target is 200 index participants and their household/whānau members who participate with them, and the primary analyses will be intention to treat on index participants.

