Participants and their whānau are planning to live together for the duration of the study	Current pregnancy or breastfeeding, or planning to conceive during the study (due to impact on interpreting outcome measures)
Access to the internet at home	Unstable body weight (active weight loss/gain >5 kg in prior three months)
Able and willing to attend all site visits	Gastrointestinal disorder that alters the digestion and absorption of nutrients (e.g., ulcerative colitis, Crohn’s disease, coeliac disease, an ileostomy or colostomy).
Willing to adhere to local health and safety regulations	Severe food allergies (anaphylaxis) in any household/whānau member
For the consumer insights study, there needs to be a willingness to be interviewed	Medication use – current use of medications that modify blood sugar levels, or anticipated regular use of oral or injected steroids
	Does not agree to refrain from donating blood for three months prior to each study visit (due to impact on HbA1c)
	Is participating in, or has recently participated in another research study involving an intervention which may alter outcomes of interest to this study
	Any other condition or situation, which in the view of investigators would affect the compliance or safety of the individual taking part

^*^Additional whānau/household members, if they are eligible and interested, may also be enrolled as an index participant.

**Table 2 tab2:** Inclusion criteria for household/whānau participants and exclusion criteria for household/whānau participants who provide a blood sample.

Living in the same household as the index individual	Age ≤ 11 years
Consent/assent to consume the intervention food	Pre-existing Type 1 diabetes.
	Chronic severe renal disease (eGFR <30 mL/min/1.72m^2^)
	Current pregnancy or breastfeeding, or planning to conceive during the study (due to impact on interpreting outcome measures)
	Unstable body weight (active weight loss/gain >5 kg in prior three months)
	Gastrointestinal disorder that alters the digestion and absorption of nutrients (e.g., ulcerative colitis, Crohn’s disease, coeliac disease, an ileostomy or colostomy).
	Medication use – current use of medications that modify blood sugar levels, or anticipated regular use of oral or injected steroids
	Does not agree to refrain from donating blood for three months prior to each study visit (due to impact on HbA1c)

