### Assignment of interventions

#### Allocation sequence generation in RCT 1 and in RCT 2 (Spirit 16a)

Index participants and their household/whānau will be block randomized into RCT 1 at site level to either start the intervention package or continue usual dietary intake for 12 weeks. If there is a second person within the household/whānau who meets the criteria for an index participant, they will be allocated to the same arm as the first index participant, where applicable. Index participants will be randomized using a computer-generated sequence. Household/whānau members will be randomized to the same arm as their corresponding index participant. Index and household/whānau participants will all be randomized once their data have been collected at Visit 2. It is not possible to blind index participants or their household/whānau members to the intervention in RCT 1. Nor is it practical to blind study staff collecting data, however the principal investigator, study statistician and the laboratory team will remain blinded throughout the study and analysis period. Participants will be informed of which arm of RCT 2 they are randomized to after they have completed the RCT 1 intervention.

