## Discussion

This trial has been designed to investigate the effect of the Mediterranean dietary pattern incorporating high quality New Zealand foods, implemented using elements of behavior science, on the cardiometabolic health of people in Aotearoa New Zealand. The trial has a number of strengths, the first of which relates to the trial design which is an efficient way to answer three separate but linked important questions which is important in the reduction of participant burden and overall research costs. It comprises two RCTs and a longitudinal cohort study which allows the effect of the 12-week combined intervention package (RCT 1) and then subsequent ongoing online social support (RCT 2) to be tested. This is then followed by testing of whether any dietary changes and effects on cardiometabolic health are maintained at 12 months through a longitudinal cohort study.

The inclusion of household/whānau participants, including any children over 5 years in the household/whānau is important when considering the impact of the dietary intervention on cardiometabolic health, where shared genetics and/or environmental factors influence health outcomes. Not only do household/whānau participants receive the study food, which is likely to improve uptake and adherence for the index participant, but the household/whānau participants are also included in the measurements, allowing an assessment of whether their health status can also be improved. Furthermore, in this study we are providing a substantive proportion of the whole household/whānau weekly food requirements in order to reduce barriers to change from cost and availability, and to increase the opportunity for trying new foods and facilitate change in dietary pattern. While other studies have provided food to facilitate adherence to an intervention (13, 35), the current study provides up to 75% of estimated energy requirements across all food groups in a way that aligns with the NZMedDiet pattern. We have demonstrated that the approach of both a household/whānau based intervention and the provision of food for a whole diet intervention is acceptable and culturally relevant for people in Aotearoa New Zealand in our feasibility study (23).

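### The primary ANCOVA for RCT 1 treats index participants from one household as independent although they share an allocation, so its standard error is too small to the extent that such households are enrolled

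*Protocol article*

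**What the plan says.** Four statements in the protocol article bear on this.

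- **Who can be an index participant.** The footnote to Table 1 reads: "Additional whānau/household members, if they are eligible and interested, may also be enrolled as an index participant". One household can therefore contribute two or more people to the primary analysis set.
- **How they are allocated.** Under the allocation sequence heading (Spirit 16a), a second qualifying person is not randomised separately: "they will be allocated to the same arm as the first index participant, where applicable".
- **How the primary outcome is analysed.** The Abstract states that "the primary analyses will be intention to treat on index participants". Statistical analyses gives the model for RCT 1 and RCT 2 as "Analysis of Covariance (ANCOVA) with the baseline value of the MetSSS as a continuous covariate and the randomized treatment as the main explanatory variable". No household term is named.
- **Where clustering is modelled.** It appears only in a different, secondary analysis: "Another important secondary analysis will be of all participants treating each household as a cluster and using a Mixed Linear model".

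The sample size section uses a t-test on individuals (difference 0.4, standard deviation 0.83, 90% power, two-sided 0.05). It gives 184, raised to 200 index participants, with no design effect.

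**The concern.** When two people are allocated together and their outcomes are correlated, they carry less information about the treatment difference than two people allocated separately. An ANCOVA without a household term counts them as two independent units. Its standard error is then too small, its confidence interval too narrow and its p-value too low.

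The article itself gives grounds to expect a positive correlation. The Discussion describes households as a setting "where shared genetics and/or environmental factors influence health outcomes", and in RCT 1 the household receives the same delivered food. Adjusting for each person's own baseline MetSSS removes correlation in starting level. It does not remove correlation in the response to a shared intervention.

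At stake is the validity of the confirmatory test of the primary outcome. The authors recognised household clustering and planned for it in a secondary analysis, but that leaves the primary test unprotected.

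**Working it through.** **1. Reproduce the plan's own figure.** Inputs from the sample size section: difference 0.4, SD 0.83, power 0.90, two-sided alpha 0.05. The standardised difference is 0.4/0.83 = 0.482. The two-sample t-test (noncentral t) needs 91.45 per arm, rounded up to 92, so 184 in total, with power 0.902. The stated 184 is reproduced, and it assumes independent individuals.

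**2. Design effect.** For households of varying size m, all members in one arm:

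DE = 1 + ICC × (Σm²/Σm − 1)

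With 200 index participants and k two-index households (all others contributing one), Σm = 200 and Σm² = (200 − 2k) + 4k = 200 + 2k. So Σm²/Σm − 1 = 2k/200 = f, the share of index participants who live in two-index households, and

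DE = 1 + f × ICC

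Here ICC is the residual household correlation in MetSSS after baseline adjustment.

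**3. Consequences of ignoring it.**

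- Reported SE / true SE = 1/√DE
- Actual two-sided alpha = 2 × (1 − Φ(1.96/√DE))
- Sample size matching the planned power = 184 × DE, rounded up

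**4. Results.** Neither f nor ICC is in the article; every value of f and ICC below is an assumption.

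| f (pairs among 200) | ICC | DE | SE understated by | Actual alpha | Power at 184 | N needed |
|---|---|---|---|---|---|---|
| 0.1 (10) | 0.1 | 1.01 | 0.5% | 5.1% | 0.899 | 186 |
| 0.1 (10) | 0.3 | 1.03 | 1.5% | 5.3% | 0.893 | 190 |
| 0.2 (20) | 0.3 | 1.06 | 2.9% | 5.7% | 0.884 | 196 |
| 0.4 (40) | 0.3 | 1.12 | 5.5% | 6.4% | 0.867 | 207 |

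Worked example for f = 0.2, ICC = 0.3: DE = 1 + 0.2 × 0.3 = 1.06; √1.06 = 1.0296; 1.96/1.0296 = 1.904; alpha = 2 × (1 − Φ(1.904)) = 0.057.

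The power and N columns use the t-test basis of the plan, without the gain from baseline adjustment.

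**5. Check by simulation.** The stated ANCOVA was run on 184 participants with allocation by household and no treatment effect, 20,000 runs per setting. The rejection rate was 0.050 with no pairs, 0.054 at f = 0.1 and ICC = 0.3, and 0.059 at f = 0.2 and ICC = 0.3. This agrees with the formula.

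**The case against.** **The size may be trivial.** The article treats co-index enrolment as a contingency. A second index participant must meet all of Table 1, including MetSSS above 0.35 and no diabetes. If such people are at most 10% of index participants and the ICC is at most 0.3, the standard error is understated by no more than 1.5% and alpha stays at or below about 5.3%. This stands, and it limits severity. It does not change the direction of the error.

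**Large inflation is not supported.** A reader might infer a type I error of 8% or more. That needs, for example, 60 two-index households (120 of 200 index participants, f = 0.6) and an ICC of 0.5 after baseline adjustment: DE = 1.30, alpha 8.6%. Nothing in the article supports such values. The Discussion's remark about shared genetics and environment concerns health outcomes in general and gives no residual correlation.

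**The sentence on few clusters is not a fault.** Of the secondary mixed model, the article says: "If in the event there are very few clusters, the random effect may not be estimable and then this will be equivalent to ANCOVA". A reader might take this as permission to drop an estimable household effect. It describes what the mixed model reduces to when the household variance cannot be estimated, and the next sentence commits to reporting the ICC when it can be. It also concerns a secondary analysis.

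**RCT 2 is uncertain.** The heading over the same-arm rule covers both trials, but the text beneath it describes household block randomisation into RCT 1, and the rule ends with a loose qualifier. The RCT 2 intervention section speaks of randomising participants. If co-index members could be split between arms in RCT 2, this error would not arise for them there. Asserting it for RCT 2 goes beyond the text.

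**Power is probably adequate.** The sample size section notes that baseline adjustment should make a smaller effect detectable. As an illustration, a baseline correlation of 0.5 multiplies the variance by 1 − 0.25 = 0.75, and 0.75 × 1.12 = 0.84, still below 1. That answers a complaint about power. It does not answer the type I error.

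**The statistical analysis plan might deal with this.** It is not shown. But the article fixes the primary model, and what it expressly defers to that plan is further effect modifiers.

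**Conclusion.** The point holds for the primary analysis of RCT 1. Multiple index participants per household are allowed, a second one takes the first one's arm, and the primary ANCOVA has no household term. Its standard error is too small whenever such households are enrolled and the residual household correlation is positive.

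The size depends on two quantities that the article does not give. Under modest assumptions (f of 0.1 to 0.2, ICC of 0.1 to 0.3) actual alpha is about 5.1% to 5.7%; at f = 0.4 and ICC = 0.3 it is about 6.4%. If no co-index participants are enrolled, there is no error. For RCT 2 the conclusion is conditional on the same-arm rule applying there. This is a modest flaw in a confirmatory test, worth correcting because the correction is easy. It is not evidence that the trial is materially underpowered or its primary test badly invalid.

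**What to change.** Amend the primary index-participant model, before any analysis, in one of two ways:

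1. Keep all index participants and fit the ANCOVA with a household random intercept, or with household-clustered standard errors. If the household variance is estimated at zero, keep clustered standard errors.
2. Restrict the primary set to the first index participant in each household, and keep the others for the all-participants analysis.

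Also state whether co-index participants share an allocation in RCT 2, and apply the same treatment there if they do.

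The cost is one sentence in the analysis section and one statement in the SAS code. No new data are needed: the data management section already links household members' identification numbers to their index participant. Option 1 gives a slightly wider interval when co-index participants are enrolled. Option 2 reduces the number analysed, so the recruitment target would have to be counted in households.

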**Figure 2 fig2:**
[figure not shown]
Formulae used for the calculation of the MetSSS.

Tables 1, 2 show the eligibility criteria for both index participants and household/whānau participants. Screening will occur consistent with our feasibility study (23). Potential participants who respond to advertisements or who otherwise contact researchers will be directed to the trial website^1^ and an on-line questionnaire to complete as step one of the two step screening process. The website provides information about the trial and the questionnaire includes contact information and questions to enable calculation of the AUSDRISK (24). If this score is greater than 12, potential participants will be invited to a second step of screening which is conducted in-person at one of the study sites. This will include a fasting blood sample and anthropometric measurements to enable the calculation of the MetSSS. If they have a fasted MetSSS greater than 0.35, they will be the index participant. Once identified, and having given written consent for participating, household/whānau members of the index participant will also be invited to participate in the trial. Between one and five household/whānau members per index participant will be invited. The food provision intervention (see below) will be calculated based on the total number of people in the household, for up to 6 members. All household/whānau members who qualify for inclusion will complete age-appropriate questionnaires (Table 3), will be invited to undertake clinical measurements and to provide blood samples if aged 11 years and over. If an index participant and household/whānau participant were to separate over the course of the trial, attempts would be made to gather data from those who continue living in the same building as the index participant.

**Table 1 tab1:** Inclusion and exclusion criteria for index participants.

Inclusion criteria	Exclusion criteria
18–70 years	Previous bariatric surgery, or pre-existing Type 1, or Type 2 diabetes. Where a previous diagnosis of T2DM is uncertain, this will be defined as ever having had two consecutive HbA1c results ≥50 mmol/mol that are at least three months apart
Metabolic syndrome severity Score (MetSSS) >0.35	Total cholesterol ≥8 mmol/L
1–5 household/whānau members agree to participate*	Chronic severe renal disease (eGFR <30 mL/min/1.72m^2^)

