Assessments								
Height	✓							
Clinical measurements^a^	✓	✓			✓	✓	✓	✓
Body composition		✓			✓	✓	✓	✓
Current medications	✓	✓		✓	✓	✓	✓	✓
Adverse events			✓	✓	✓	✓	✓	✓
Fasting blood samples ^b^	✓	✓			✓	✓	✓	✓
Fecal sample		✓			✓	✓	✓	

^a^Weight, waist circumference, height, blood pressure in triplicate. ^b^HbA1c, fasting glucose, lipids and metabolites and hormones related to metabolic health Household/whanau members will attend visits 2, 3a/3b, 4, and 5.

A number of sub-studies may be undertaken which include consumer insights including that of Pacific island participants; mixed meal tolerance tests; use of a phone application for the measurement of dietary intake; fecal microbiome analyses. Details of these sub-studies will not be described in this paper.

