### Sample size (Spirit 14)

The sample size uses a clinically important difference of 0.4 for the MetSSS score based on detecting a ‘moderate’ effect size. This is because the MetSSS score was designed to represent the total number of standard deviations different for an overall risk factor profile for poor cardiovascular outcomes (19, 34). The standard deviation for the MetSSS for the calculation, 0.83, was derived from a large Auckland-based cohort study of these risk factors in a similar sample to that for recruitment (20). A t-test based sample size calculation used 90% power and a two-sided type I error rate of 0.05 was for 184 total participants and increased to 200 index participants to allow for a 10% non-completion rate. A smaller effect size is likely to be detectable by using baseline MetSSS as a co-variate in an ANCOVA.

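### RCT 1 collects two pre-randomization MetSSS values but adjusts for only the last; entering both could give a small, assumption-dependent gain in precision at no sampling cost

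*Protocol article*

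**What the plan says.** The Eligibility criteria section describes the in-person screening step: "This will include a fasting blood sample and anthropometric measurements to enable the calculation of the MetSSS". A value above 0.35 qualifies the person as an index participant. Table 5 (Details of outcome measures) ticks the row "Fasting blood samples ^b", and the row for clinical measurements, at Visit 1 and again at Visit 2. The section on allocation sequence generation places the RCT 1 randomization after the Visit 2 data are collected. Every index participant should therefore have two complete MetSSS values before being randomized.

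The Statistical analyses section specifies an ANCOVA with randomized treatment and a single continuous baseline MetSSS, and fixes which value that is: "The baseline measurement will be just before the relevant randomization". For RCT 1 this is Visit 2. The article gives the Visit 1 value no role beyond eligibility.

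The Sample size section works with "90% power and a two-sided type I error rate of 0.05" and a "clinically important difference of 0.4 for the MetSSS score". It adds that baseline adjustment should allow a smaller difference to be detected, but does not quantify this.

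**The concern.** MetSSS is built from fasting glucose, triglycerides, HDL cholesterol, systolic blood pressure and waist circumference. If a single reading is an imperfect measure of a person's usual level, a second pre-randomization reading carries extra information about the week-12 outcome. The protocol already follows this logic within a visit, where it averages repeated weight, waist and blood pressure readings.

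Both values precede randomization, so adjusting for both cannot bias the treatment comparison, and selecting on Visit 1 does not change that. What is at stake is the width of the confidence interval and the power for differences below 0.4. The Discussion makes such differences relevant, since it expects small effects on several risk factors.

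**Working it through.** **1. The plan's own figure.** Inputs from the Sample size section: difference 0.4; "The standard deviation for the MetSSS for the calculation, 0.83"; two-sided 0.05; 90% power. The allocation ratio is not stated ("will be block randomized into RCT 1 at site level"), so 1:1 is assumed.

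Normal approximation: n per arm = 2(1.960 + 1.282)² × 0.83² / 0.4² = 90.5, so 91. The exact noncentral t needs 92 per arm, or 184 in total, with power 90.2%. The stated 184 reproduces. It uses the unadjusted SD, so it takes no credit for any baseline covariate.

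**2. Assumptions, none of them in the protocol.** Write ρ12 for the Visit 1–Visit 2 correlation, ρ1Y and ρ2Y for each visit's correlation with week 12, and μ for the mean MetSSS among people screened. Take trivariate normality with SD 0.83 at each visit before selection.

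**3. Formulae, allowing for entry only if Visit 1 > 0.35.** Let σ² = 0.83² = 0.6889, a = (0.35 − μ)/0.83, λ = φ(a)/(1 − Φ(a)) and k = 1 + aλ − λ². After selection each covariance becomes S_ij = σ²[ρ_ij − (1 − k)ρ_1i ρ_1j].
- Residual variance, Visit 2 only: S_YY − S_2Y²/S_22.
- Residual variance, both visits: σ²(1 − R²), unaffected by the selection. When ρ1Y = ρ2Y = ρ, R² = 2ρ²/(1 + ρ12).

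Worked case: ρ12 = 0.8, ρ = 0.7, μ = 0.3. Then a = 0.060, λ = 0.837 and k = 0.3505.
- S_22 = 0.6889(1 − 0.6495 × 0.64) = 0.4025
- S_2Y = 0.6889(0.7 − 0.6495 × 0.56) = 0.2316
- S_YY = 0.6889(1 − 0.6495 × 0.49) = 0.4696
- Visit 2 only: 0.4696 − 0.2316²/0.4025 = 0.336
- Both visits: 0.6889(1 − 0.98/1.8) = 0.314
- Reduction: 1 − 0.314/0.336 = about 7%

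**4. Three settings, if Visit 1 predicts week 12 as well as Visit 2 does.** SE = √(2 × variance/92). The difference detectable at 90% power is 3.242 × SE.

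| ρ12 / ρ / μ | Residual variance | Reduction | SE | Detectable difference |
|---|---|---|---|---|
| 0.9 / 0.7 / 0.3 | 0.347 to 0.334 | 4% | 0.087 to 0.085 | 0.281 to 0.276 |
| 0.8 / 0.7 / 0.3 | 0.336 to 0.314 | 7% | 0.086 to 0.083 | 0.277 to 0.268 |
| 0.8 / 0.75 / 0.6 | 0.288 to 0.258 | 10% | 0.079 to 0.075 | 0.256 to 0.243 |

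The SE shrinks by 1 − √(1 − reduction), which is about 2%, 3% and 5%.

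**5. If Visit 1, being further from the outcome, predicts week 12 less well.**
- ρ1Y lower than ρ2Y by 0.05: the reductions fall to about 0.3%, 3% and 4%.
- Lower by 0.10: about 1% or less in all three settings.
- Full decay with time (ρ1Y = ρ12 × ρ2Y): zero.

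**6. The upper end.** With ρ12 = 0.7, ρ = 0.8 and μ = 0.6, the residual variance with both visits is 0.6889(1 − 1.28/1.7) = 0.170, against 0.217 with Visit 2 only, a reduction of about 22%. This corner needs week 12 to correlate more strongly with each earlier visit than those two visits correlate with each other.

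**7. Averaging compared with separate covariates.** Without selection and under full decay with r = 0.7 (so the Visit 1–week 12 correlation is 0.49), the average leaves 1 − (0.49 + 0.7)²/(2 × 1.7) = 0.583 of the outcome variance. Visit 2 alone leaves 1 − 0.49 = 0.51. Averaging would thus raise residual variance by about 14%, whereas two separate covariates would leave it unchanged.

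**The case against.** The strongest objection is that nothing here is an error. ANCOVA on the last pre-randomization value is a valid and clearly prespecified analysis, with no bias, ambiguity or type I error problem. That stands.

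Nor does the trial need the precision to meet its stated aim. At the design difference of 0.4 with 92 per arm, the single-baseline residual variances in step 4 already give power of 99.6%, 99.6% and 99.9%. Adding Visit 1 moves these to 99.7%, 99.8% and 99.96%. That also stands, given the assumed correlations.

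The size of the gain cannot be verified. The protocol gives no within-person correlation, no interval between Visits 1 and 2 and no mean for those screened, and a modest drop in Visit 1's predictive value removes most of the benefit. This is why the range must start at zero.

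Two stronger readings are tempting. One is that the plan throws the Visit 1 value away and so leaves known biological noise in the primary comparison. The document does not support it: the value serves eligibility, and no day-to-day variability figure is given. The other is that RCT 2 loses precision in the same way by ignoring values earlier than Visit 3b. Those values predate the diet package and are not repeat measurements of the Visit 3b state. They would also come from different visits in the two former RCT 1 arms (Visit 2 or Visit 3a). Whether they predict drift after food provision ends is conjecture, and no gain has been calculated.

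What survives is narrow: the article itself fixes the primary covariate, and a second eligible covariate already exists.

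**Conclusion.** The point holds as an optional, low-cost refinement of RCT 1. Using only Visit 2 is valid and does not endanger the stated power, but it may leave precision unused. A fair statement of size is roughly 0 to 10% of residual variance, or a standard error about 0 to 5% smaller. It could be larger if the Visit 1–Visit 2 correlation is low while both visits predict week 12 well, and it is about nil if correlation decays with time. All of this rests on assumed correlations, an assumed screened mean and normality; only the SD of 0.83 and the 0.35 cut-off come from the protocol. A reader should not infer bias, an underpowered trial or a demonstrated loss in RCT 2.

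**What to change.** Before any unblinded analysis, state that the RCT 1 primary ANCOVA includes the Visit 1 and Visit 2 MetSSS as two separate continuous covariates, and do the same for MetSSS components measured at both visits. Do not average them. Visit 1 is truncated at 0.35 and its mean is raised by selection, and an average forces equal weights that lose precision if the older value predicts less well. Keep Visit 2 alone as the reference for descriptive change from baseline, since Visit 1 was used for selection.

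For RCT 2, the pre-intervention MetSSS (Visit 2, or Visit 3a for former RCT 1 controls) may be added as a separate covariate beside Visit 3b if the team wishes.

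The cost is one sentence and one degree of freedom, with no extra visits or samples.
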